#### Circadian rhythm assessment

The circadian rhythm variable consists of two components: subjective questionnaires and objective behavioral data. The questionnaires used include the Morningness Eveningness Questionnaire (MEQ), the Pittsburgh Sleep Quality Index (PSQI), and the Seasonal Pattern Assessment Questionnaire (SPAQ). The MEQ is a 19-item self-rating scale used to evaluate chronotype, with scores indicating evening, intermediate, or morning types [35]. The PSQI is an 18-item self-rating scale that assesses sleep quality and disturbances, and a validated Chinese version will be used [36,37]. The SPAQ is a widely used questionnaire for evaluating seasonal effects on mood and behavior. It includes a general seasonality score (GSS) that can be used to screen for seasonal affective disorder (SAD) [38,39]. Except for the SPAQ, all the aforementioned scales and questionnaires have already been validated or translated into Chinese versions.

On the day of evaluation, participants will be asked to wear a wrist-worn actigraph device (wGT3X-BT, v1.9.2, ActiGraph LLC) for 14 consecutive days and nights. The actigraph’s flashing light will be disabled throughout the monitoring period. The device will continuously record physical activity, sleep/wake information and sedentary time using a sampling frequency of 100 Hz. Participants will be instructed to continuously wear the actigraph except during activities such as showering, swimming, or any activity that would consistently expose the device to water for more than 30 min. Data retrieval and analyses will be performed using the ActiLife software program (version 6.13.4) with 60-second epochs [40]. The collected raw data will be stored and analyzed using publicly available algorithms. Non-wear time will be defined as 60 consecutive minutes of zeros with a 2-minute spike tolerance based on the default Wear Time Validation algorithm provided by Actilife 6.13.4. Any non-wearing epochs will be excluded from the analysis without any data imputation [41,42]. For a day to be deemed valid, it must have a minimum of 20 h of wearing time [42]. A participant will be considered valid if they have a minimum of 7 valid days, including at least 5 weekdays and 2 weekend days [35].

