The circadian rhythms of sleep-wake activity will be calculated using Cole-Kripke Algorithm in Actilife [43,44]. We will retrieve sleep parameters such as Sleep Onset (SO), Total Sleep Time (TST), Wake after Sleep Onset (WASO) and Sleep Efficiency (SE). SO means the first minute that the algorithm scores ‘asleep’. TST equals to the total number of minutes scored as ‘asleep’. WASO means the total number of minutes the subject was awake after SO occurred. SE represents the number of sleep minutes divided by the total number of minutes the subject was in bed (i.e. the difference between the In-Bed and Out Bed time) [44].

The circadian rhythm parameters of physical activity will be calculated using the specialized GGIR package for R software [45]. Non-parametric circadian rhythm analysis will be employed. We aim to determine the intradaily variability (IV), interdaily stability (IS) and relative amplitude (RA) of the rest-activity rhythms [43,46,47]. IV refers to the consolidation of rest-activity states within a day, where higher values indicate greater fragmentation of the rhythm with more transitions between rest and active states [45]. IS describes the consistency of rest-activity patterns across different days, with higher values indicating greater stability [48]. RA represents the difference in activity between the most active 10-hour period (M10) and the least active 5-hour period (L5) and serves as a marker of amplitude strength [46]. Time of sedentary and moderate-to-vigorous physical activities (MVPA) will also be calculated based on validated activity cut-points in Actilife [35,49,50].

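### Sleep with the device off shortens total sleep time and, on the literal definition, lowers sleep efficiency, because no wear requirement applies within the night

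*Protocol article*

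**What the plan says.** All the rules are in the protocol article under Circadian rhythm assessment.

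- Detection of non-wear: "Non-wear time will be defined as 60 consecutive minutes of zeros with a 2-minute spike tolerance".
- Handling: "Any non-wearing epochs will be excluded from the analysis without any data imputation".
- Valid day: "For a day to be deemed valid, it must have a minimum of 20 h of wearing time". Nothing is said about where in the 24 h the other time may fall.
- Valid participant: "A participant will be considered valid if they have a minimum of 7 valid days, including at least 5 weekdays and 2 weekend days".
- TST: "TST equals to the total number of minutes scored as ‘asleep".
- SE: "SE represents the number of sleep minutes divided by the total number of minutes the subject was in bed", with the denominator spelled out as "the difference between the In-Bed and Out Bed time".

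The Statistical analysis section then asks whether changes in circadian rhythm predict changes in neurocognitive functioning. The covariates it gives as examples are disease duration, age, gender, medication, education and symptom severity. Wear time is not among them.

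**The concern.** A minute without the device cannot be scored as sleep. TST has no denominator, so each minute slept with the device off is lost from it. SE has a denominator, but it is a difference between two clock times, and deleting epochs in between moves neither of them. Read literally, the numerator loses the unworn sleep and the denominator keeps it.

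The valid-day rule does not prevent this. A day may lack up to 24 − 20 = 4 h, and nothing stops those hours from lying in the night. The multiple imputation or expectation maximisation named under Statistical analysis would not obviously reach it either: such a day counts as valid, so its TST and SE enter as observed values that are too low, not as missing values.

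At stake is the meaning of a change in TST or SE between visits. If participants wear the device less faithfully at 6 or 12 months, sleep appears to have worsened. If faithful wear also goes with mood or cognition, that artefact can correlate with cognitive change. This link is an assumption. It is plausible here, since the sample size section allows for 50% dropout and the Discussion gives low motivation without payment as the reason for not using a sleep diary.

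**Working it through.** The article gives no SE or TST figure, so there is nothing of its own to reproduce. The check applies its definitions to an assumed night.

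**Inputs from the article:** non-wear is flagged from 60 min of zeros; non-wear epochs are dropped; a valid day has at least 20 h of wear; recording lasts 14 days; at least 7 valid days are needed.

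**Assumptions:** 480 min in bed; true SE 85%, so 0.85 × 480 = 408 min asleep and 72 min awake; visit values are means over nights.

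**Formulas**, for *d* minutes off in bed, of which *s* were sleep:
- TST = 408 − s
- literal SE = (408 − s) / 480
- SE with non-wear removed from both terms = (408 − s) / (480 − d)

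| Minutes off in bed | What was lost | TST (min) | Literal SE | SE, non-wear out of both terms |
|---|---|---|---|---|
| 0 | – | 408 | 85.0% | 85.0% |
| 60 | in proportion, s = 51 | 357 | 74.4% | 85.0% |
| 60 | all sleep, s = 60 | 348 | 72.5% | 82.9% |
| 60 | all wake, s = 0 | 408 | 85.0% | 97.1% |
| 120 | in proportion, s = 102 | 306 | 63.8% | 85.0% |
| 240 (limit of the valid-day rule) | in proportion, s = 204 | 204 | 42.5% | 85.0% |

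With a proportional loss, the relative fall in TST and literal SE is d/480 whatever the true SE: 12.5% for 60 min. A true SE of 80% becomes 70.0%, and one of 87.5% becomes 76.6%. With 600 min in bed and a true SE of 80%, 60 min off gives 72.0%, a fall of 10%.

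**Averaged over a recording.** With *k* affected nights out of *N*, the relative fall is (k/N) × d/480.
- 60 min off on 4 of 14 nights: (4/14) × 12.5% = 3.6%. Mean SE falls by 85 × 0.0357 = 3.0 points and mean TST by 51 × 4/14 = 14.6 min.
- 60 min off on 4 of 7 nights (the minimum number of valid days): (4/7) × 12.5% = 7.1%.
- 60 min off on 1 of 7 nights: (1/7) × 12.5% = 1.8%.

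A participant with full wear at baseline and the 4-of-14 pattern at 12 months would thus show about 3 points less SE and 15 min less sleep with no change in sleep.

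**Which part depends on the reading.** If the exclusion of non-wear epochs is taken to cover the SE denominator too, SE follows the last column and the proportional bias disappears. The TST column is the same under either reading.

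**The case against.** The strongest reply is that the mismatch in SE is inferred. The exclusion of non-wear epochs is not limited to the numerator, and a condensed article may rely on the full protocol to say that in-bed time is counted net of non-wear. That reading is possible, but it does not fit the denominator as the article spells it out, so the two statements need reconciling. It also does nothing for TST.

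The second reply is that the behaviour is hypothetical. Only removal in bed affects TST and SE, whereas the plan says "Participants will be instructed to continuously wear the actigraph except during activities such as showering, swimming", and such removals mostly fall outside bed time. A short shower need not reach the 60-min threshold either. This stands: no removal for sleep is foreseen, and losses of 120 to 240 min in a night are upper bounds, not expectations.

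The third reply is that the damage is limited. The Statistical analysis section does not single out SE or TST as the predictor. The argument does not touch intradaily variability, interdaily stability or relative amplitude. The primary outcome is the cognitive composite, and the authors call the study exploratory. This also stands, and it keeps the point in proportion.

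A reader might go further and infer that all the minute measures are raw totals, so that device removal always looks like poor sleep or low activity. The article does not support that. For sedentary and moderate-to-vigorous activity it says only that their time will be calculated; whether this is scaled to wear may be left to the full plan. The direction would also be wrong for two measures: lost wake minutes lower WASO, which looks like better sleep, and lost sedentary minutes make a person look less sedentary.

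**Conclusion.** The point holds for TST under either reading of the exclusion rule, and for SE when its definition is taken literally. With 8 h in bed, a true SE of 85% and minutes lost in proportion to sleep and wake, one night with 60 min off loses 12.5% of both measures, and 4 such nights in 14 lower the mean by about 3.6%. These figures rest on assumed nights and assumed removal; the documents give no data on wear. If the missing minutes were wake in bed, TST and literal SE are unaffected.

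The documents do not support reading this as a definite miscalculation across all the sleep and activity measures, or as a typical halving of SE. The 42.5% figure marks only what a valid day would permit. Nor do they establish that wear goes with cognition; that is what would turn an artefact in the exposure into a spurious association. The point is worth settling before the actigraphy measures are derived, because the remedy is cheap.

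**What to change.** 1. Add a wear criterion within the night, on top of the 20-h day rule. Nights with any detected non-wear between In-Bed and Out Bed time are left out of the averages for TST, WASO and SE, or kept only in a sensitivity analysis. A tolerance below 60 min would add little, because the detection rule flags nothing shorter and a bout lying wholly in the night would fail it anyway.
2. On any such night that is kept, subtract non-wear minutes from the SE denominator, so that the SE definition and the exclusion rule agree.
3. Say whether the requirement of 7 valid days, including 2 weekend days, also applies to the nights that remain, and report wear time by visit.
4. As a clarification only, say whether sedentary and moderate-to-vigorous time are totals, daily means or shares of waking wear time.

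The cost is a few sentences and re-processing of stored raw data; no new measurements are needed. Some nights are lost from the sleep averages, which matters most for participants near the 7-day minimum. Step 2 has a bias of its own: if the missing minutes were wake in bed, it overstates SE (97.1% instead of 85% in the 60-min example). Step 1 should therefore carry the main analysis.

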#### Neurocognitive assessment

The primary outcome will be a comprehensive cognitive composite score. Neurocognitive functioning will be evaluated using the Cambridge Neuropsychological Test Automated Battery (CANTAB), developed by Cambridge Cognition in Cambridge, UK (www.camcog.com) [51]. The tests have undergone validation in studies involving healthy human volunteers as well as various patient groups in the fields of behavioral and psychopharmacological research [52,53]. These tests will be administered on the same day as the actigraph wearing. The selected tests, including Delayed Matching to Sample (DMS), Paired Associates Learning (PAL), Rapid Visual Information Processing (RVP), and Spatial Working Memory (SWM), assess different cognitive domains [54–56]. DMS and PAL evaluate visual memory, RVP measures sustained attention, and SWM reflects executive function. By converting the results of these four tests into Z-scores, the scores of each participant on different cognitive domains can be derived, and a composite cognitive functioning score can be calculated [57,58].

### Sample size calculation

The sample size for this study was determined based on the primary hypothesis. To calculate the sample size, a review of relevant literature was conducted, and the PASS.15 computer software was used. Due to limited available reports, data from a previous study that evaluated changes in SWM between errors after 1 month of olanzapine treatment in 15 unipolar/bipolar depressive patients was used. In that study, the between errors at baseline and 1-month olanzapine treatment were 34 ± 24 and 21 ± 21, respectively (Mean ± Standard Deviation) [59].

With an assumed power of 0.80 and an alpha level of 0.05, it was determined that a cohort size of 41 at follow-up would achieve 80% power to detect a difference of −13 between the null hypothesis (both baseline and 12-month follow-up means of SWM errors are 34) and the alternative hypothesis (mean of 12-month follow-up is 21). The estimated standard deviations were 21 and 21 at baseline and 12-month follow-up, respectively, using a two-sample *t*-test [54]. Considering a potential dropout rate of 50% and the decision not to replace dropout participants, a total of 81 patients at baseline were deemed necessary. Finally, given the large number of outpatient receptions, we plan to recruit 100 participants.

Therefore, the study aimed to recruit a sample size of 100 patients at baseline to account for potential dropouts and achieve the desired statistical power.

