Interestingly, exploring circadian rhythm influence on neurocognitive functioning seems feasible with potential pathophysiological inspirations [13]. Recent studies focusing on Alzheimer’s and other neurodegenerative diseases have speculated on the involvement of seasonal cognitive plasticity and circadian rhythm disruption in neurocognitive functioning changes [14–17]. Additionally, a few pieces of evidence also support such an association with mental disorders [18]. For instance, rats subjected to chronic jet lag simulation demonstrated enhanced depressive behaviors and cognitive deficits [19]. Large-scale UK Biobank data revealed an association between disrupted circadian rhythmicity in mood disorders and cognitive function [20]. Moreover, the ‘desynchronization effect’ resulting from evening chronotypes and circadian disruption might render individuals vulnerable to cognitive and psychiatric challenges [21]. Furthermore, certain molecules are believed to play a role in both circadian rhythm disruption and neurocognitive impairment, mediated through mechanisms like immune-inflammatory activities [22,23].

Regrettably, up to this point, no study has been found that focuses on the long-term clinical correlation between circadian rhythm and neurocognitive functioning in BD patients. Exploring such a correlation holds utmost importance because, if the speculation proves true, 1) it could aid in identifying patients with a worse cognitive prognosis through circadian rhythm evaluation, enabling early intervention when necessary; 2) it may open up new possibilities for treating neurocognitive impairment in BD, for example, from a rhythmic perspective, such as brain synchronization; 3) it would provide stronger evidence supporting the pivotal role of circadian rhythm in BD pathophysiology [24].

Therefore, this study protocol was designed to bridge the current research gaps by investigating the predictability of neurocognitive functioning through circadian rhythm in BD. The objective of this study is to assess whether circadian rhythm could predict the long-term change in neurocognitive functioning among BD patients. It is hypothesized that circadian rhythm could predict the long-term change in neurocognitive functioning.

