### Statistical analysis

SPSS (version 26) will be used for the analysis of this study. Histograms will be used to determine the normality or approximate normality of the data. This will be achieved by combining them with the Shapiro-Wilk test [60]. Descriptive analyses will be performed to examine participant and disease characteristics, as well as data from clinical, circadian rhythm, and neurocognitive functioning assessments. Missing value analyses will be conducted with multiple imputation or expectation maximization methods to handle any missing data.

Spearman correlations will be employed to compare subjective and objectively assessed circadian rhythm patterns. Subjective assessments include MEQ, SPAQ, and PSQI results, while objective assessments will primarily rely on behavioral data.

Longitudinal analyses will involve calculating changes in SAS, SDS, HAMD, HAMA, and YMRS scores, and correlating these difference scores (baseline minus 6-month follow-up, baseline minus 12-month follow-up) with circadian rhythm parameters for each participant using Spearman correlation. Mixed regression models will be used to determine if changes in circadian rhythm significantly predict changes in neurocognitive functioning from baseline to 6-month follow-up and 12-month follow-up [61]. Stepwise adjustment of covariates will be employed to construct several regression models to explore the robustness of the relationship between circadian rhythm and neurocognitive functioning. Adjustments will be made for other factors that may influence these associations, such as disease duration, age, gender, current medication use, education level, and severity of emotional symptoms.

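### The stated 80% power is for a fall in mean SWM errors; it does not apply to the primary hypothesis or the composite outcome, and power for these is not established

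*Protocol article*

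**What the plan says.** The protocol article describes the basis of the sample size and the study's question in four places.

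- **Sample size calculation:** "The sample size for this study was determined based on the primary hypothesis". The input is "data from a previous study that evaluated changes in SWM between errors after 1 month of olanzapine treatment in 15 unipolar/bipolar depressive patients", with between errors of 34 ± 24 before and 21 ± 21 after treatment. The null is that "both baseline and 12-month follow-up means of SWM errors are 34"; the alternative is a 12-month mean of 21. On standard deviations: "The estimated standard deviations were 21 and 21 at baseline and 12-month follow-up, respectively". A two-sample t-test gives 41 at follow-up, and a 50% dropout allowance gives 81 at baseline. Recruitment is set at 100, and the section closes by saying that this number secures the power wanted.
- **Introduction:** "It is hypothesized that circadian rhythm could predict the long-term change in neurocognitive functioning".
- **Neurocognitive assessment:** "The primary outcome will be a comprehensive cognitive composite score". It is built from Z-scores on DMS, PAL, RVP and SWM.
- **Statistical analysis:** "Mixed regression models will be used to determine if changes in circadian rhythm significantly predict changes in neurocognitive functioning", from baseline to 6 and 12 months, with stepwise covariate adjustment.

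**The concern.** A mean change over time and a predictor of who changes more are different quantities. The null in the sample size section could be tested without any participant wearing an actigraph. Power for that test says nothing about power to find a link between circadian rhythm and cognition. The endpoint differs too: one component test was used in place of the four-test composite.

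The borrowed effect is also a poor match. It is a 1-month change on a specified drug in depressed unipolar and bipolar patients. It is applied here to a 12-month observational cohort that admits remitted patients and, apart from barring electroconvulsive therapy, sets no treatment requirement.

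What is at stake is how a null result will be read. A reader who takes the section at its word could treat a non-significant circadian finding as the result of a study with 80% power for that question. The plan does not support that reading.

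**Working it through.** **1. Reproduce the plan's figure.** Inputs from the Sample size calculation section: difference 13, SD 21 at both times, and "With an assumed power of 0.80 and an alpha level of 0.05". Sidedness is not stated; two-sided is assumed.

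n per group = 2 × (1.960 + 0.842)² × 21² / 13² = 2 × 7.849 × 441 / 169 = 40.96, so **41**. This matches the plan. An exact t calculation gives 42, with 79.1% power at 41.

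Dropout: 41 / (1 − 0.5) = 82, against 81 stated; the difference is immaterial.

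The figure therefore reproduces as a comparison of two means of SWM errors. No association parameter enters it.

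**2. Set the calculation beside the question.**

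| | Sample size section | Study's primary question |
|---|---|---|
| Outcome | SWM between errors | Four-test composite |
| Circadian variable | None | The predictor |
| Quantity tested | Mean change, 34 to 21 | Association with cognitive change |
| Method | Two-sample t-test | Mixed regression |

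**3. Show what the planned size gives for an association.** The article states no effect size for the association, so a range of r is **assumed**. A simple correlation among completers, with Fisher's z and a two-sided 5% test, stands in for the mixed model. Completers: 100 × (1 − 0.5) = 50.

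- Smallest r with 80% power = tanh[(1.960 + 0.842) / √(n − 3)]. For n = 50: tanh(2.802 / 6.856) = **0.39**. For n = 41, the calculated minimum: tanh(2.802 / 6.164) = 0.43.
- Power ≈ Φ(√(n − 3) × atanh r − 1.960), plus a negligible opposite tail. Example, n = 50 and r = 0.3: 6.856 × 0.3095 = 2.122; 2.122 − 1.960 = 0.162; Φ = 0.564.
- Completers needed for 80% power = (2.802 / atanh r)² + 3, rounded up. For r = 0.3: (2.802 / 0.3095)² + 3 = 84.9, so 85.

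| Assumed r | Power, n = 50 | Power, n = 41 | Completers needed for 80% |
|---|---|---|---|
| 0.2 | 28% | 24% | 194 |
| 0.3 | 56% | 48% | 85 |
| 0.4 | 83% | 74% | 47 |
| 0.5 | 96% | 92% | 30 |

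**4. Sensitivity.** Six covariates are named in the Statistical analysis section. Counting only the degrees of freedom they use (n − 9 in place of n − 3), the detectable r at n = 50 moves from 0.39 to 0.41. With no dropout at all (n = 100) it is 0.28.

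**5. Side points that do not change the conclusion.** The source study's baseline SD is 24, but 21 was used. With 24 and 21, n = (1.960 + 0.842)² × (24² + 21²) / 13² = 47.2, so 48, and power at 41 is 74%. The two-sample test also treats repeated measures on the same patients as independent groups. A paired test at an assumed within-patient correlation of 0.5 would need about 23.

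**The case against.** The strongest reply is that nothing shows the study to be underpowered. A reader might infer from the mismatch that the trial lacks 80% power for its own question. The documents do not support that. They give no effect size for the association, and the Discussion says there is little on which to predict the results. At r = 0.4 or above, 50 completers give more than 80% on the approximation used here. This part of the reply stands.

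Three further points also stand:

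- A completers-only correlation is a stand-in. The planned mixed model uses two follow-up visits, imputation or expectation maximization is foreseen for missing data, and participants who miss month 6 may still attend month 12. The planned analysis could do somewhat better. Multiplicity control across the several circadian parameters would push the other way.
- Covariate adjustment does not necessarily cost power. Covariates that explain outcome variance can raise it.
- The plan is to enrol 100, so 50 completers is the fairer reference than 41.

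The authors could also say that the section openly shows what was powered, that few reports were available, and that the Discussion calls the study exploratory. These remarks soften the risk of misreading, but they do not correct the claim. Scarce literature explains a weak input, not a calculation for a different hypothesis. An exploratory aim argues for a statement of precision rather than an 80% power claim tied to a primary hypothesis.

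**Conclusion.** The point holds as a mismatch. The 80% power belongs to a before-after difference of −13 in mean SWM errors. It does not apply to the primary hypothesis or the composite outcome, so the statement that the sample size rests on the primary hypothesis is wrong as written. Power for the actual question is not established and could lie on either side of 80%. With about 50 completers the dividing line is a true correlation of about 0.39, or 0.41 if six covariates cost only their degrees of freedom. At r = 0.3 the association would be missed in roughly 44% of such studies (1 − 0.56).

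These figures rest on a two-sided 5% test, 50% dropout, a single circadian parameter, and a simple correlation in place of the mixed model. They illustrate scale and are not the study's own detectable effect. Because a stated power is wrong and text alone can correct it, it should be corrected.

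**What to change.** In the Sample size calculation section, delete the sentence that ties the calculation to the primary hypothesis, and the closing conclusion that 100 patients give the desired power for it. If the SWM calculation is kept, label it as applying to a mean change in SWM errors only.

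Add a statement for the association that the Statistical analysis section tests, for example:

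> With 100 enrolled and 50% dropout (about 50 completers), and using a simple correlation between change in a circadian parameter and change in the composite score as an approximation to the mixed model (two-sided 5%), the study has 80% power for a correlation of about 0.39. Under assumed correlations of 0.2, 0.3, 0.4 and 0.5, power is about 28%, 56%, 83% and 96%. Associations will be reported with 95% confidence intervals, and a non-significant result will not be read as absence of an association.

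The authors should also reconcile the predictor. The Introduction speaks of circadian rhythm predicting later cognitive change, while the Statistical analysis section uses change in circadian rhythm. The replacement text must name whichever predictor is primary.

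The cost is a text change and a less favourable stated power. Enrolment stays at 100 and no analysis needs to be added.

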## Methods and analysis

### Setting and recruitment

This study follows a longitudinal cohort design, as depicted in Figure 1, with participant evaluations scheduled at baseline, 6-month follow-up, and 12-month follow-up after recruitment. Participants who miss the 6-month follow-up will still be eligible for the 12-month follow-up assessment. Ethical approval was obtained from the Research Ethics Committee of the First Affiliated Hospital of Chongqing Medical University (Approval Number: 20227001). Furthermore, this study has been registered with the Chinese Clinical Trial Registry under the registration code ChiCTR2200064922 on 21 October 2022. The study will be conducted in accordance with the Declaration of Helsinki [25].

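### The sample size calculation enters a baseline SD of 21 where its source gives 24, and uses an independent two-sample t-test for one cohort measured twice, so 41 does not follow from the quoted data

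*Protocol article*

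**What the plan says.** All the figures are in the Sample size calculation section of the protocol article.

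- Source data, from a small study of olanzapine in depressed patients: "the between errors at baseline and 1-month olanzapine treatment were 34 ± 24 and 21 ± 21, respectively", labelled there as mean ± SD.
- Design values: "With an assumed power of 0.80 and an alpha level of 0.05", with 41 patients at follow-up, which "would achieve 80% power to detect a difference of −13 between the null hypothesis" (mean 34 at both times) and the alternative (mean 21 at 12 months).
- SDs and test: "The estimated standard deviations were 21 and 21 at baseline and 12-month follow-up, respectively, using a two-sample" t-test.
- Dropout: with 50% loss and no replacement, "a total of 81 patients at baseline were deemed necessary". Recruitment is then set at 100.

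The Setting and recruitment section fixes the design: "This study follows a longitudinal cohort design", with the same participants assessed at baseline, 6 months and 12 months.

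**The concern.** Two things in the paragraph do not fit together.

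First, both means and the follow-up SD pass unchanged from the source into the calculation. Only the baseline SD changes, from 24 to 21. No reason is given, and the change lowers the required number.

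Second, the quantity being powered is a change within the same patients, but a two-sample t-test treats the two sets of scores as independent groups. The power of the within-patient comparison depends on the correlation between a patient's two scores, and the calculation has no place for it.

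This is the only power justification in the article. A reader who starts from the quoted data and the described design cannot arrive at 41.

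**Working it through.** **Inputs.** Difference 13 (34 − 21), alpha 0.05, power 0.80, SDs 21/21 as entered and 24/21 as quoted, dropout 50%: all from the Sample size calculation section. Sidedness is not stated. Two-sided is assumed, because it reproduces 41, whereas one-sided by exact t gives 33. The within-person correlation r is not given, so a range is shown.

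**1. The plan's own figure (two-sample, SDs 21/21).**
n = (1.960 + 0.842)² × (SD₁² + SD₂²) / 13²
= 7.849 × (441 + 441) / 169 = 40.96, so 41.
Power at 41 is 80.0% by normal approximation. By the exact noncentral t it is 79.1%, and 42 are needed. The stated figure reproduces to within one patient.

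**2. Same test, quoted SDs (24/21).**
n = 7.849 × (576 + 441) / 169 = 47.2, so 48 by normal approximation and 49 by exact t.
Power at 41 is 74.2% (normal) or 73.2% (exact t).
With 50% dropout, 49 / 0.5 = 98 at baseline.

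**3. Paired t-test, quoted SDs.**
SD of the change = √(24² + 21² − 2 × r × 24 × 21) = √(1017 − 1008r). Power is by exact noncentral t with n − 1 degrees of freedom.

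| r (assumed) | SD of change | Power at 41 | Completers for 80% | Power at 50 |
|---|---|---|---|---|
| 0 | 31.9 | 72.1% | 50 | 80.7% |
| 0.1 | 30.3 | 76.5% | 45 | 84.5% |
| 0.2 | 28.6 | 81.2% | 40 | 88.4% |
| 0.3 | 26.7 | 86.0% | 36 | 92.1% |
| 0.5 | 22.6 | 94.8% | 26 | 97.8% |
| 0.7 | 17.6 | 99.6% | 17 | 99.9% |

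Power at 41 crosses 80% at r of about 0.18.

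**4. Dropout step.** 41 / (1 − 0.5) = 82. The stated 81 leaves 40.5.

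**5. Planned recruitment.** 100 × 0.5 = 50 completers. With SDs 24/21, power at 50 is 81.4% for the two-sample test and 80.7% for the paired test at r = 0. It is higher at every positive r in the table.

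**The case against.** A reader might infer that the claim of 80% power at 41 is false. The article does not support that. The figure reproduces from the inputs actually entered, apart from the small gap between the normal approximation and exact t. The 73% figure arises only if the SD is corrected while the unsuitable independent test is kept. With both corrections made, 41 is enough unless r is below about 0.2, and for repeated scores in the same patients a positive correlation makes the two-sample choice conservative. This stands, and it limits the point: 41 is untraceable to the quoted data, but not shown to be too small.

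A reader might also infer that the study is under-enrolled. It is not, for this comparison: 50 completers suffice in every case examined. The Discussion also describes the study as exploratory.

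It can be said, too, that 21 may be deliberate. The sentence speaks of estimated SDs and cites a different reference from the one giving 34 ± 24, and what that reference supports cannot be seen here. So the substitution is an unexplained inconsistency rather than a proven entry error. It still needs a reason, because the paragraph presents the olanzapine study as the data used.

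The 81 against 82 discrepancy is a rounding slip of one patient and carries no weight alone.

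Finally, a corrected paired calculation would still power a mean change in SWM errors, whereas the stated hypothesis is that circadian rhythm predicts cognitive change. That is a separate matter, which this correction does not settle.

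**Conclusion.** The concern holds in limited form. The baseline SD entered (21) contradicts the one quoted (24) without explanation, and the two-sample t-test does not fit a before-and-after comparison in one cohort. Taken alone, the SD correction lowers power at 41 from about 79–80% to about 73–74% and raises the need to 48–49. Taken together with pairing, the requirement runs from 50 completers at r = 0 to 17 at r = 0.7, so whether 41 suffices depends on a correlation that the article does not state.

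This rests on a two-sided 5% test, a true difference of 13, the quoted SDs carrying over to 12 months, and r of 0 or more. The consequence is a sample size justification that cannot be traced to its data. It is not a shortfall in the planned 100.

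**What to change.** Restate the paragraph as a paired t-test for a change of 13 with SDs 24 and 21, or keep 21 at baseline and give the reason and source. State that the test is two-sided. State the assumed within-person correlation and show the result over a range that includes 0, for example 0 to 0.7. Then give the number of completers and divide by (1 − 0.5) for the baseline number; if 41 is kept, that is 82. At r = 0 the calculation gives 50 completers and 50 / 0.5 = 100 at baseline, so recruitment stays at 100 and would be justified by the calculation itself.

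The cost is one re-run in the same software and the rewording of one paragraph. Design, visits and enrolment do not change.
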